### Outcomes

2.9

The primary outcome of the trial will be the variation in the 6-minute walk test by week 24 as compared to baseline. The assessment of 6MWT will be performed in accordance with standardized procedures. The test will be conducted in a 30-meter corridor, and standardized instructions and encouragement will be provided to all participants. To ensure patient safety and consistency, predefined stopping criteria including intolerable dyspnea, chest pain, dizziness, or any other symptoms indicating potential risk, as judged by the assessor, will also be applied. The use of walking aids or supplemental oxygen will be permitted if clinically necessary, and the use will be recorded to minimize variability. Moreover, all outcome assessors will remain blinded to treatment allocation throughout the study to reduce measurement bias. The same assessor will evaluate a given participant across study visits to reduce inter-rater variability. All assessors will receive standardized training prior to study initiation. The 6MWT will be performed 1–2 h after routine medication administration to minimize variability. Duplicate tests will not be performed unless clinically indicated.

The secondary outcomes will include: (1) major adverse cardiovascular events (MACE, including cardiac death, non-fatal myocardial infarction, and rehospitalization due to HF) at 3 and 6 months. All major adverse cardiovascular events and heart failure-related rehospitalizations will be reviewed and adjudicated by an independent committee blinded to treatment allocation; (2) BNP levels at week 24 compared with baseline; (3) NYHA class functional classification at week 24 compared with baseline; (4) quality of life score of the Kansas City Cardiomyopathy Questionnaire at week 24 compared with baseline.

Other exploratory outcomes will include: (1) clinical outcomes including diuretic dosage, and 24-hour fluid intake and output (recorded for inpatients only); (2) TCM syndrome scale scoring; (3) cardiac structure outcomes including left ventricular ejection fraction, diastolic diameter, interventricular septal thickness, and posterior wall thickness indicated by echocardiography. Image acquisition and measurements will follow predefined procedures, and all echocardiographic data will be interpreted by experienced cardiologists who are blinded to treatment allocation to minimize assessment bias; (4) biochemical measurement outcomes including lipid profile (including total cholesterol, triglycerides, high-density lipoprotein cholesterol, low-density lipoprotein cholesterol, apolipoprotein A1, apolipoprotein B, and homocysteine), myocardial enzymes [including lactic dehydrogenase, creatine kinase (CK), and CK-MB], inflammation indicators [including C-reactive protein (CRP) and interleukin-6 (IL-6)] and other biochemical parameters (including bioactive adrenomedullin, CD146, vasopressin 2 receptor, cyclic adenosine monophosphate, protein kinase A, aquaporin 2, mucin 16, stromelysin 2, and soluble stromelysin 2). Specifically, bioactive adrenomedullin and CD146 are associated with endothelial function and vascular integrity, reflecting microcirculatory dysfunction. Vasopressin 2 receptor and aquaporin 2 are involved in water metabolism and fluid retention, representing fluid imbalance. Cyclic adenosine monophosphate and protein kinase A are key components of intracellular signaling pathways related to neurohormonal activation. In addition, stromelysin 2, soluble stromelysin 2, and mucin 16 are associated with extracellular matrix remodeling, inflammation, and tissue injury. Together, these biomarkers provide a comprehensive evaluation of endothelial dysfunction, fluid regulation, and neurohormonal activation, which are closely related to heart failure progression and may potentially reveal the mechanism of FJHQG in treatment of HF. Blood plasma will be gathered and kept at −80 °C in the lab freezer for analysis. Exploratory outcomes will be interpreted descriptively and will not be used for confirmatory inference.

### Safety assessment

2.10

Safety evaluations will be performed during Visits 1, 3, and 4, including standard tests of blood, urine, stool, and functions of the liver, kidneys, and coagulation system. Laboratory abnormalities will be evaluated based on severity grading and clinical significance. The drug will be discontinued in the event of serious adverse events, intolerable adverse reactions, or clinically significant abnormalities in liver, renal, or hematologic parameters, as judged by the investigator.

### Adverse events

2.11

In the course of the trial, adverse events (AEs) will be defined as unforeseen or harmful clinical situations. In the event of such occurrences, patients will receive immediate intervention. The ethics committee will receive comprehensive reports on all aspects of AEs within 24 h. The relationship between AEs and the study drug will be assessed as definitely related, possibly related, possibly unrelated, definitely unrelated, or indeterminate.

### Data collection and management

2.12

Data will be initially recorded using paper-based case report forms (CRFs). All CRFs will be subsequently entered into an electronic data management system by independent data administrators. Double data entry and cross-validation will be also performed to ensure data accuracy and completeness. Original paper CRFs will be securely archived for verification. Methods including double data entry, data cleaning, manual verification, and additional validation techniques will be used to verify the data's validity, accuracy, and completeness. Due to the relatively small sample size, a formal Data and Safety Monitoring Board will not be established. Nonetheless, participant safety will be monitored throughout the study by the principal investigators and the institutional ethics committee, with all adverse events reviewed and reported in accordance with Good Clinical Practice guidelines.

### Researcher education and assurance of quality

2.13

Researchers will receive a prepared Standard Operating Procedure (SOP). Every researcher will receive training to guarantee uniformity. The program encompasses evaluating qualified participants, employing survey instruments, among other activities. The WeChat group will aim to foster connection among patients. To maintain high standards, the quality control team and monitors from Hangzhou Hospital of TCM will conduct frequent inspections.

A protocol will be created for researchers at every facility to guarantee uniformity and standardization. Researchers will complete detailed training that covers screening eligible participants, administering survey scales, performing the 6-minute walk test, and other methods. A WeChat group will also be utilized to facilitate close communication with patients. The quality control team and inspectors designated by Hangzhou Hospital of TCM will carry out routine oversight. Monitoring activities will be implemented to ensure adherence to the study protocol and data integrity. The study team will conduct regular reviews of informed consent documentation, case report forms, and study drug accountability. Participant safety will be monitored throughout the trial, with adverse events evaluated and recorded at each visit.

To ensure the quality and consistency of the trial, roles and responsibilities of researchers are clearly assigned. Investigators are responsible for patient recruitment, clinical assessment, intervention implementation, and outcome evaluation. Data administrators independently conduct data entry, verification, and management. Clinical monitors perform regular on-site monitoring visits according to SOP to ensure adherence to the study protocol, accuracy of case report forms, and completeness of source data documentation. Monitoring activities include verification of informed consent, drug accountability, and outcome assessments. In addition, all clinical laboratory assessments are conducted using standardized procedures in certified laboratories to ensure consistency and reliability of results.

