### Study design

2.1

This trial is a part of the project “Theoretical Research on Treating HF with TCM Compatibility Formula - Topic Five Group Distribution Combination Theory Research” (2018 YFC1704505), led by Tianjin University of Traditional Chinese Medicine. The Hangzhou Hospital of Traditional Chinese Medicine, acting as the appointed clinical trial unit, hosts the clinical trial. The investigation will be conducted in accordance with Good Clinical Practice standards and the ethical principles of the Helsinki Declaration (11, 12). The research will follow the SPIRIT guidelines for interventional trials (13). Additionally, it will strictly adhere to the guidelines set forth by the 2017 CONSORT-CHM Formulas for Chinese Herbal Medicine (14).

This is a randomized, double-blind, placebo-controlled trial. The study will take place at Hangzhou Hospital of TCM and will include two stages: a 12-week treatment phase and a subsequent 12-week follow-up phase after intervention. A total of 100 patients with HF will be randomly assigned to two groups equally. On the basis of conventional drug therapy, the intervention group will receive treatment with FJHQG, while the placebo group will receive the corresponding placebo of FJHQG. Figure 1 depicts the study design.

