### Randomization and blinding

2.6

This is a single-center study conducted at Hangzhou Hospital of TCM. Randomization will be performed by an independent statistician who is not involved in patient recruitment, intervention, or outcome assessment. The randomization sequence will be generated using SAS software version 9.4, with a 1:1 allocation ratio, stratified by sex, and age, utilizing random block sizes of six. Allocation concealment will be ensured using a centralized system, and researchers, participants, and data administrators and statisticians will be unaware of the randomization and treatment allocations. To ensure the blinding of participants and investigators, the placebo is identical to FJHQG in appearance, color, taste, packaging. Emergency unblinding will only be performed when necessary for patient safety and must be approved by principal investigator, and all such events will be documented.

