### Follow-up visits and monitoring schedule

2.8

The study will start with a 7-day preliminary phase where eligible individuals will provide their consent and initial information will be gathered. Future appointments will be planned for 6 days ± 1 day (visit 1), 4 weeks ± 3 days (visit 2), and 12 weeks ± 3 days (visit 3) after starting the treatment. Follow-up assessments will be conducted at Week 12 ± 7 days post-discontinuation of treatment (24W ± 7d) (visit 4). To minimize loss to follow-up, participants will be regularly contacted through telephone calls and WeChat group communication. Reminders will be provided before each scheduled visit to improve retention and adherence. Table 1 outlines the comprehensive assessment timetable.

**Table 1 T1:** Schedule of enrollment, interventions, and assessments.

Study phase time	Lead-in period	Treatment period			Follow-up period
	Screening (−7D-0D)	Baseline (6D ± 1d)	Week 4 (4W ± 3d)	Week 12 (12W ± 3d)	Week 24 (24W ± 7D)^a^
Patients					
Eligibility screen	X				
Inclusion/exclusion criteria	X				
Informed consent	X				
General information	X				
Medical history	X				
Allocation	X				
Pregnancy examination	X				
Outcomes					
Primary outcome					
6-minute walk test	X	X	X	X	X^c^
Secondary outcomes					
BNP	X	X	X	X	X
MACE (including cardiac death, non-fatal myocardial infarction, and rehospitalization due to heart failure) ^b^	X	X	X	X	X
NYHA classification	X	X	X	X	X
KCCQ quality of life score	X	X	X	X	X
Exploratory outcomes					
Diuretic usage		X	X	X	X
Echocardiography	X			X	X
Heart failure-related rehospitalization rate^b^	X	X	X	X	X
TCM syndrome score	X	X	X	X	X
Myocardial enzyme levels	X			X	X
Inflammatory markers and other biochemical indicators	X			X	X
Safety					
Vital signs	X	X	X	X	X
Biochemical indexes	X			X	X
Electrocardiogram results	X			X	X
Adverse events	X	X	X	X	X
Others					
Drug distribution	X		X		
Drug recycle			X	X	
Combined medication			X	X	
Confirmation of medication compliance		X	X	X	X

a Visit 4 corresponds to the follow-up assessment conducted at Week 24, which is 12 weeks after completion of the 12-week treatment period, as stated in manuscript.

b Continuous monitoring throughout the study.

c Primary endpoint assessed at week 24.

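### A WeChat group stated to connect patients with each other would mix both arms and works against participant blinding; any resulting bias is of unknown size

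*Protocol article*

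**What the plan says.** The protocol article mentions WeChat three times.

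- Section 2.13, first paragraph, gives a patient-to-patient purpose: "The WeChat group will aim to foster connection among patients".
- Section 2.13, second paragraph, gives a staff-to-patient purpose: "A WeChat group will also be utilized to facilitate close communication with patients".
- Section 2.8 uses it for retention: "participants will be regularly contacted through telephone calls and WeChat group communication".

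The design statements it must fit with are in 2.1 ("This is a randomized, double-blind, placebo-controlled trial") and 2.6 ("This is a single-center study conducted at Hangzhou Hospital of TCM"). On who is blinded, 2.6 says that "researchers, participants, and data administrators and statisticians will be unaware of the randomization and treatment allocations". The stated safeguards are a placebo matched in appearance, colour, taste and packaging (2.6, 2.7) and, in 2.9, that "all outcome assessors will remain blinded to treatment allocation throughout the study".

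**The concern.** Blinding of participants depends on each patient having no good comparator. A patient alone cannot easily tell whether a change in urine output or breathlessness is more than placebo patients experience. A group that brings patients together supplies that comparator. If some participants come to believe they are on active granules and others that they are on placebo, and those beliefs follow true allocation to some degree, effort and self-report can drift apart between the arms without any true treatment effect.

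The outcomes differ in exposure. The 6MWT (primary) depends on effort, and 2.9 recognises this by standardising encouragement. KCCQ is self-reported. NYHA class rests partly on reported symptoms. BNP is a laboratory value and MACE is adjudicated by a blinded committee, so both are much less exposed.

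**Working it through.** **1. Would the group contain both arms?** The article does not say so outright; it follows from three statements. There is one centre (2.6), hence one pool of patients. No division of the group by arm is described. Researchers are blinded (2.6), so those running the group could not divide it by arm without knowing the allocation. A shared group is therefore mixed.

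**2. Do the stated safeguards close this route?** Matching of the placebo hides the product, so comparing sachets should tell participants little. It does not hide perceived effects. The article itself leads one to expect some: the Discussion cites earlier work with the decoction reporting more 24-hour urine and symptom relief, and the Introduction cites reduced diuretic use. Blinded assessors protect the measurement but not what participants believe when they walk or fill in a questionnaire.

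**3. Do the three mentions agree?** Two describe contact between staff and patients. One describes contact among patients. Only the former is needed for the retention purpose given in 2.8.

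**4. Planning figures (2.14).** Difference 50 m, SD 72 m, two-sided alpha 0.05, power 90%.

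- Normal approximation: n per arm = 2 × (1.960 + 1.282)² × 72² / 50² = 43.6, so 44.
- With the noncentral t, power is 89.6% at 44 and 90.3% at 45. The stated 45 per arm is reproduced.
- Dropout: 45 / 0.90 = 50 per arm, 100 in total, as stated.

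The sample size is not affected by this point.

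**5. What a bias would do, under assumption.** The documents give no size for an expectancy bias. Assume a true difference of zero and a net between-arm bias b.

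- Standard error at 45 per arm: 72 × √(2/45) = 15.18 m.
- Two-sided rejection rate, normal approximation: 1 − Φ(1.96 − b/SE) + Φ(−1.96 − b/SE).

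| Assumed b | b/SE | Normal approximation | Noncentral t, 88 df |
|---|---|---|---|
| 0 m | 0 | 5.0% | 5.0% |
| 5 m | 0.33 | 6.3% | 6.2% |
| 10 m | 0.66 | 10.1% | 10.0% |
| 15 m | 0.99 | 16.7% | 16.5% |

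At 50 per arm (SE = 72 × √(2/50) = 14.4 m), the normal approximation gives 6.4%, 10.7% and 18.1% for 5, 10 and 15 m. For scale, 15 m is half of the 30 m that 2.14 calls clinically meaningful. Adjusting for baseline 6MWT, age and sex (2.15) would not remove such a bias, because it arises after randomisation.

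**The case against.** The strongest reply is that the point rests on one sentence, which may be loose wording. The first two paragraphs of 2.13 largely repeat each other, and the sentence on connection among patients may be a poor rendering of communication with patients. Settings, moderation and posting rules may also sit in an SOP that is not shown. This stands as a caution, and the absence of such rules is not the complaint. But the sentence as printed sets an aim that conflicts with participant blinding, and if it is a slip it should be corrected. A group channel in which patients can see each other's posts would leave some of the concern in place either way.

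Several stronger inferences are tempting, and the documents do not support them:

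- *That comparing the granules would unblind patients.* The placebo is described as identical in appearance, colour, taste and packaging.
- *That perceived effects would reveal allocation.* They would do so only if the product has noticeable effects. The Introduction cites small observations without significant adverse events. The primary 6MWT is also measured at week 24, 12 weeks after treatment stops, when on-treatment cues may have faded.
- *That any shared belief biases the result.* A belief held equally in both arms cancels in the difference; only a differential one matters.
- *That assessor blinding fails through the group.* Section 2.13 says "Investigators are responsible for patient recruitment, clinical assessment, intervention implementation, and outcome evaluation", so those who deliver treatment may also assess outcomes. But nothing says that they would read patients' posts, and posts would show symptoms and events already recorded at visits, not allocation.
- *That loss of independence between patients damages the analysis.* No effect on the arm comparison can be shown from the documents.

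**Conclusion.** The point holds as a risk to participant blinding, created by a stated aim and not by an omitted detail. It rests on the inference that a shared group would be mixed, which the single centre and blinded staff make strong, and on the possibility that perceived effects differ between arms. It concerns the 6MWT and KCCQ, NYHA class in part, and BNP and adjudicated MACE very little.

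Its size is unknown. The rise in the error rate to about 6%, 10% and 16–17% for 5, 10 and 15 m is an illustration at SD 72 m and 45 per arm; it would apply to any bias of that size and does not measure harm from WeChat. It also supposes no true effect on walking distance together with cues clear enough to shift belief by arm, which is possible but narrow. A reader might infer that the blind will be broken or the primary result invalidated; the documents do not show that. A correction is justified because the risk is easily avoided before the data exist and cannot be removed by analysis afterwards.

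**What to change.** In 2.8 and 2.13, describe WeChat contact as one-to-one messages, or as a broadcast-only channel in which participants cannot see or post to each other. Delete the sentence in 2.13 on fostering connection among patients, so that all mentions of WeChat describe staff-to-patient contact only.

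The cost is a change of messaging setting, small edits to the text, somewhat more staff time for individual messages, and the loss of peer contact. Reminders and retention contact are kept, and the sample size and analysis do not change.

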### Sample size calculation

2.14

Patients will be randomized in a 1:1 ratio to receive either FJHQG or placebo. Previous studies in HF suggested that improvements of approximately 30 meters in the 6MWT is clinically meaningful. According to our previous clinical observation, assuming FJHQG demonstrates an improvement of 50 meters in 6MWT compared with placebo and a standard deviation of 72 meters among two groups, a two-sided significance level of *α* = 0.05, and a statistical power of 90%. The results indicate that at least 45 patients will be needed per group. Considering an anticipated dropout rate of 10%, a total of 100 patients will be enrolled, with 50 allocated to the intervention group and 50 to the placebo group. The study is powered for the primary functional endpoint and is not designed to detect differences in clinical events.

### Statistical analysis

2.15

All statistical analyses will be conducted on both the intention-to-treat (ITT) and per-protocol (PP) populations. The ITT population will include all randomized participants, while the PP population will consist of participants with at least 80% adherence to the protocol. Continuous variables following a normal distribution will be presented as means ± standard deviations (SD) with 95% confidence intervals (CI), and non-normally distributed variables will be reported as medians with interquartile ranges (IQR) and analyzed using non-parametric methods. Between-group comparisons for normally distributed continuous variables will use the independent samples t-test, and for non-normal distributions, the Wilcoxon rank-sum test. Within-group comparisons will employ paired t-tests or Wilcoxon signed-rank tests as appropriate. Categorical variables will be summarized as counts and percentages, with between-group comparisons using the Chi-square or Fisher's exact test, and within-group comparisons using the McNemar test. Baseline characteristics will be reported descriptively without significance testing to assess comparability between groups. Differences in background treatment between groups will be summarized descriptively and adjusted for in the statistical analysis to reduce potential confounding.

The primary outcome (6-minute walk test) will be analyzed using analysis of covariance (ANCOVA) with baseline values and key covariates (age, sex) as covariates to adjust for potential confounding. Secondary outcomes, due to their diverse nature, will be analyzed using appropriate methods: continuous variables with t-test or Wilcoxon test, categorical variables with Chi-square or Fisher's exact test, and repeated measures or longitudinal data using linear mixed-effects models. To control for multiple comparisons among secondary outcomes, the false discovery rate (FDR) adjustment using the Benjamini-Hochberg method will be applied, and a hierarchical structure will be applied with the primary outcome taking precedence over secondary and exploratory outcomes. The primary analysis will be conducted according to the intention-to-treat (ITT) principle, including all randomized participants. If the proportion of missing 6MWT data is 5% or greater, missing data for the 6MWT will be handled using multiple imputation under the missing-at-random assumption. The imputation model will include baseline 6MWT value, age, sex, and treatment group as predictors. Imputation will be performed using a single model based on all available data without separating treatment arm. In addition, reasons for missing data will also be recorded, categorized, and summarized descriptively, and will be compared between groups. Prespecified subgroup analyses will be conducted based on heart failure phenotype, defined by left ventricular ejection fraction (LVEF ≥50% vs. <50%), and by sex. These subgroup analyses will be considered exploratory. Sensitivity analyses will be performed, including per-protocol analyses and complete-case analyses, to assess the robustness of the results. Deaths occurring before the final assessment will be handled in sensitivity analyses using a worst-case approach by assigning a value of zero for the 6MWT, representing the worst functional outcome. Adverse events will be summarized in tables and compared between groups using descriptive statistics. All analyses will be performed using SAS software version 9.4, and two-tailed *P*-values < 0.05 will be considered statistically significant. A detailed statistical analysis plan will be finalized prior to database lock to ensure prespecified analysis procedures.

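### Section 2.15 plans significance tests of change within each arm without calling them descriptive; they cannot support an efficacy statement, and the risk is to secondary reporting

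*Protocol article*

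**What the plan says.** The general methods paragraph of Section 2.15 (Statistical analysis) gives a between-group test for each type of variable and adds a within-group test. For continuous variables: "Within-group comparisons will employ paired t-tests or Wilcoxon signed-rank tests as appropriate". For categorical variables: "within-group comparisons using the McNemar test". The paragraph ties these tests to no particular outcome and gives them no stated role. It also runs all analyses in both the intention-to-treat and the per-protocol population.

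The next paragraph sets one threshold for all analyses: "two-tailed *P*-values < 0.05 will be considered statistically significant". It makes a between-arm ANCOVA, adjusted for baseline, age and sex, the primary analysis of the six-minute walk test (6MWT). Secondary outcomes get t-tests or Wilcoxon tests, chi-square or Fisher's exact tests, or mixed models, with Benjamini-Hochberg adjustment across secondary outcomes and precedence for the primary outcome. Within-group tests are not mentioned in that rule.

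Elsewhere the article says plainly when a result is only descriptive. It does so for baseline characteristics and adverse events (Section 2.15) and for exploratory outcomes (Section 2.9), and it labels the subgroup analyses exploratory. Within-group tests of the primary and secondary outcomes carry no such label.

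**The concern.** The trial randomises against placebo so that the effect of FJHQG can be read as the difference between arms. A change from baseline inside one arm also contains everything the arms share. The article gives reasons why something may be shared:

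- Entry requires a BNP floor, NYHA class II to III and a symptom-based syndrome (Sections 2.2 and 2.3), which invites regression to the mean.
- Guideline therapy is optimised for everyone, and adjustments during the study are recorded (Section 2.7).
- Walk tests are not routinely duplicated ("Duplicate tests will not be performed unless clinically indicated", Section 2.9), so familiarity with the test may contribute.

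A significant within-arm change is therefore not evidence for FJHQG. Nor is the contrast of a significant change with FJHQG and a non-significant one with placebo, because that contrast does not test the difference between arms. At week 24 alone, the 6MWT, BNP, NYHA class and KCCQ in two arms and two analysis populations give 4 × 2 × 2 = 16 within-arm tests. All carry the 0.05 threshold, and none is named in the multiplicity rule.

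**Working it through.** **The plan's own figure.** Section 2.14 assumes a 50 m difference, an SD of 72 m, two-sided 0.05 and 90% power.

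- Normal approximation: n = 2 × (1.960 + 1.282)² × 72² / 50² = 43.6, so 44 per arm.
- The t-based solution is 44.56, so 45 per arm, with power 0.903.
- Allowing for 10% dropout: 45 / 0.90 = 50 per arm.

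The stated 45 and 50 reproduce and are not in dispute.

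**Inputs for the check.**

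- 45 evaluable patients per arm (Section 2.14).
- SD of change 72 m. This is an assumption, because Section 2.14 does not say whether 72 m is the SD of the change or of the week-24 value. The range 50 to 90 m is also shown.
- Two-sided 0.05 (Section 2.15).
- No true difference between arms, and a shared mean gain m in both. The documents give no value for m, so 0 to 50 m is shown.

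**Formula.** Let q be the probability that one arm's paired t-test shows a significant gain. It comes from the noncentral t distribution with 44 degrees of freedom and noncentrality m × √45 / 72. The arms are independent, so the probability that FJHQG is significantly improved and placebo is not is q(1 − q). This cannot exceed 0.25, which it reaches at q = 0.5.

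| Shared gain m | Noncentrality | q | q(1 − q) |
|---|---|---|---|
| 0 m | 0 | 0.025 | 0.024 |
| 5 m | 0.47 | 0.066 | 0.062 |
| 10 m | 0.93 | 0.147 | 0.126 |
| 15 m | 1.40 | 0.277 | 0.200 |
| 20 m | 1.86 | 0.445 | 0.247 |
| 21.5 m | 2.00 | 0.500 | 0.250 |
| 25 m | 2.33 | 0.625 | 0.234 |
| 30 m | 2.80 | 0.780 | 0.171 |
| 40 m | 3.73 | 0.954 | 0.044 |
| 50 m | 4.66 | 0.995 | 0.005 |

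**Sensitivity to SD and n.** The ceiling of 0.25 holds for any SD and n; only its location moves. With 45 per arm it lies at 14.9 m for SD 50 and 26.9 m for SD 90. With 50 per arm and SD 72 it lies at 20.4 m. At a shared gain of 10 m (45 per arm) the probability is 0.192 for SD 50 and 0.097 for SD 90.

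**Simulation** (100,000 trials per setting, 45 per arm, SD 72, no difference between arms; the between-arm test is a two-sample t-test on change).

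| Shared gain | FJHQG only significant | Same, with between-arm test not significant | Between-arm P < 0.05, either direction |
|---|---|---|---|
| 0 m | 0.024 | 0.016 | 0.050 |
| 10 m | 0.124 | 0.104 | 0.050 |
| 21.3 m | 0.251 | 0.226 | 0.051 |
| 30 m | 0.170 | 0.149 | 0.050 |

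The between-arm test keeps its 5%, of which half (2.5%) favours FJHQG, whatever the shared gain. The contrast of two within-arm results does not.

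**The case against.** The strongest reply is that the plan nowhere proposes to infer efficacy from within-arm tests. The primary analysis is a between-arm ANCOVA under intention to treat, the tests listed for secondary outcomes are also between-arm or mixed-model methods, and the paired tests appear only in a general methods list. This stands. A reader might infer that the trial will claim efficacy from within-arm P values, or that its primary error rate is inflated; the text supports neither.

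A reader might also take one in four as this trial's false-positive rate. It is only the mathematical ceiling of q(1 − q), and reaching it needs a shared gain of about 21 m that the documents do not give. Patients must be stable on unchanged therapy for at least 2 weeks (Section 2.3), and the endpoint falls 12 weeks after treatment stops, so a small shared change is plausible and the figure could be a few percent. The calculation is also for the 6MWT, where the ANCOVA governs. For BNP and KCCQ the same formula and ceiling apply, but the documents give no inputs to place them on the curve.

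Two further inferences go too far. Exploratory measures should not be counted, because Section 2.9 already makes them descriptive and non-confirmatory. MACE has no baseline value to change from. Nor does the sentence on duplicate tests show that there is no second early walk: Table 1 lists a 6MWT at screening and another in the column headed Baseline, which Section 2.8 places about 6 days after treatment starts. How far practice enters the change is therefore open.

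Finally, it can be said that the role of within-arm P values belongs in the analysis plan, which is not shown. That would answer a complaint about missing detail. Here the article itself prescribes the tests and the threshold, so the choice is stated and open to comment.

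**Conclusion.** The point holds as a matter of secondary reporting. Section 2.15 prescribes within-arm significance tests that do not address the trial's question, calls P < 0.05 significant for them, does not label them descriptive for the primary and secondary outcomes, and does not mention them in the multiplicity rule.

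The size is uncertain. Under the stated assumptions, the misleading pattern ranges from 0.5% to 25% per outcome over shared gains of 0 to 50 m, and exceeds 10% between 10 and 30 m. The result rests on independent arms, roughly normal changes and an SD of change of 72 m.

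The sample size and the primary conclusion are untouched. It would be wrong to say that the plan will generate many false claims; it leaves room for them. This is a desirable improvement, not a condition for a valid primary result.

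**What to change.** Remove the paired t, signed-rank and McNemar within-group tests from Section 2.15. Report the mean or median change in each arm with a 95% CI, as description only. Add one sentence saying that every efficacy statement rests on the between-arm comparison. For the continuous secondary outcomes (BNP, KCCQ), adjust that comparison for the baseline value in place of the unadjusted t-test.

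This costs a deletion, a sentence and a small change of model. It needs no new data and leaves the sample size alone. It can be made now, since the article says the analysis plan will be finalised before database lock. All that is lost is a set of P values that could not support a claim about FJHQG.
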